## **9.2 Outcomes**

Section 9.1, above, contains detailed information regarding Outcomes

## **9.3 Sample Size and Accrual**

Section 9.1, above, contains detailed information regarding Sample Size and Accrual

## **9.4 Data and Safety Monitoring**

### ***9.4.1 Monitoring and Reporting Process***

The Principal Investigator is responsible for oversight of the data safety and will work with the Co-PIs to monitor the proposed study. The stopping rules for futility and efficacy are described in detail in Section 9.1.3. In summary, the trial will be stopped for futility if the trial doesn't reach accrual targets or if both ALSFRS-R and survival do not show sufficient trends towards efficacy. Also, if the dropout rate is so high that the power to show a survival benefit is minimal, then the primary endpoint of the trial will be changed to compare 12 month changes in ALSFRS-R and participants will be given the option of discontinuing study medication at 12 months. Stopping for efficacy is based upon alpha spending rules, described in Section 9.1.3.

The PI and the Steering Committee will work with the appointed DSMB to evaluate safety on an ongoing basis, and develop safety stopping rules as needed.

The DSMB will meet approximately every 6 months and at the end of the study. In addition, the DSMB will meet prior to study initiation and after completion of STAGE 1 and STAGE 2. Meetings may be conducted by teleconference at the request of the Board members. In addition, the Chairman of the Board may call ad hoc meetings. The PI will be responsible for overseeing the preparation of reports to the NINDS DSMB as well as interim communication through the program staff, should more frequency notification of safety issues be required. Summary reports of the frequency of all clinical adverse events and safety laboratory tests will be generated at pre-specified time points by the Statistical Consultant and the Coordination Center and forwarded to the DSMB for review. As necessary, the DSMB can review the frequencies of clinical and laboratory abnormalities. The DSMB will be responsible for establishing safety-stopping rules. The PI will provide some suggested safety stopping rule for consideration by the DSMB. Recommendations for modification or termination of the trial based on safety data will be made by the DSMB to the PI.

#### **9.4.2 The Medical Monitor**

The Medical Monitor will be responsible for independent review of the safety laboratory tests and adverse events. The Medical Monitor will be responsible for monitoring the real-time reporting of Serious Adverse Events, and will review laboratory reports and adverse events monthly, or more frequently as needed. He or she will be blinded to treatment assignment. If the Medical Monitor has concerns regarding the safety data, he or she may notify the DSMB.

### **9.5 Data Analyses**

Section 9.1, above, includes detailed information regarding Data Analyses

## **10. DATA COLLECTION, SITE MONITORING, AND ADVERSE EXPERIENCE MONITORING**

### **10.1 Records to be Kept and Project Organization**

The MGH Neurology Clinical Trials Unit (NCTU) Coordination Center and the Biostatistics Center at the MGH will work in close collaboration with the Neurology Clinical Research Unit at SUNY Upstate Medical University to conduct the proposed study. The project coordination, data management, biostatistics, regulatory compliance, adverse event reporting, quality assurance issues and budgetary and contract components will be coordinated from MGH. The outcome measure training and study monitoring will be conducted by SUNY Upstate Medical University. This distributed effort is due to the expertise in project coordination, data management and biostatistics for multi-center clinical trials in ALS at MGH and the expertise at SUNY Upstate Medical University in outcome measure assessment and training and study monitoring. The project coordination staff will work in collaboration with the PI and Co-PIs to accomplish all the tasks necessary for preparation and implementation of the project, including the drafting of the study protocol, development of the model consent document, IND application and annual report, assisting in communications with the Steering Committee, FDA, DSMB, developing project timelines, compiling required documents from sites, preparing the detailed manual of operations, and overseeing enrollment and enrollment projections. The project coordination staff will reply

to site protocol inquiries on a daily basis, track adverse events, study drug discontinuations and study compliance.

A trial network will be set up that will utilize the Internet, telephone conference calls, and periodic mailings as its means of communications. Also, a contact information database will be created and maintained that will be used for group/individual mailing of paper documents and to facilitate telephone and fax communication between the Coordination Center and clinical sites. A Web portal has been established to provide the study personnel with an easily accessible repository of documents, which is essential for sharing information across multiple clinical trial sites. The secure, password-protected portal will contain role-based resources for study personnel. For example, the portal provides personnel lists with contact information, the complete study protocol, model informed consent forms and other study-related documents, a list of subject accrual figures that is updated continuously to allow anyone in the group to monitor study progress, a list of frequently asked questions for quick reference, and other resources that the clinical investigators and coordinators might find useful.

The Coordination Center has selected a central laboratory for the study. This laboratory has provided its current certificate of the laboratory and the curriculum vitae of the central laboratory director to the Study PI. In addition, a table listing the ranges of values considered normal for the determinations each laboratory is performing for the trial has been provided.

## **10.2 Role of Data Management**

### ***10.2.1 Data Flow and Management Overview***

The Data Management staff at the MGH NCTU will be responsible for all aspects of data acquisition and processing, from the design of instruments used to collect data through the delivery of an accurate and timely database to the Biostatistics Center. In conjunction with the PI and the Biostatistician, the data management staff at MGH will design the electronic case report forms (eCRFs) that will capture all the data collected as part of the protocol. Interactive computer modules for real-time capture of all important study events including enrollments, serious adverse events (SAEs), reportable incidents and premature withdrawals will be created. The Electronic Data Capture and Data Management System (EDC&DM) will be tested and validated to ensure accuracy, reliability and consistent intended performance. The system conforms to the 21 CFR Part 11 and other guidance documents on computerized systems in clinical trials. The system will allow the study sites to single-enter the data via an Internet browser-based interface. The entered data will be saved in a Microsoft SQL Server database located on a server maintained by Partners Healthcare Systems IS department. Necessary documentation on the validation procedure will be maintained by the Coordination Center. A full time data manager will be responsible for the data acquisition and management at the MGH Coordination Center.

The flow of data and the data clarification process is summarized in Figure 7. The site personnel are instructed to enter information within 48 hours of the visit. An edit checking and data clarification process will be put in place to ensure accuracy and completeness of the database. Logic and range checks as well as more sophisticated rules will be built into the Web-based

forms (eCRFs) to provide immediate error checking of the data entered. The system will automatically create electronic queries on behalf of the Data Manager if saved electronic Case Report Forms (eCRFs) contain data that are out of range, out of window, missing or not calculated correctly. The Data Manager identifies the errors in the EDC system by using electronic logic checks and the Study Monitor identifies errors by direct visualization and comparison of data entered into the system with the source documents. Any inconsistent or questionable data points are queried to the sites and followed up on by both the Study Monitor and Data Manager as needed. Once the site addresses the query, the Data Manager or the Study Monitor can verify that the response is satisfactory, and that the value in the data field has been corrected. The Data Manager or Study Monitor can then “close” the query in the database. The sites and Study Monitor will only have access to the queries concerning their subjects. The Data Manager will be able to see the queries for the entire subject population. The Sites will have the ability to write a comment for a form or field. Each comment has its own history, which is recorded in a log. The log records the information that has been entered in the comment, who entered it, and when it was entered. The comment field is treated as a regular data field; hence all changes to the comments are tracked in the audit trail. We propose to use the National Cancer Institute’s (NCI) Common Terminology Criteria for Coding Adverse Events (CTCAE) version 3.0. This is a descriptive terminology, organized by body system and including specific criteria for grading severity of Adverse Events. This system will allow study coordinators to quickly search for the most relevant term for each event and will give specific criteria governing the reporting of severity for each term. With this system, the event will be coded at the site and subsequently checked by the Data Manager. The system will have predefined roles and system Administrators will assign them to the system users. Depending on the role assigned, the users will differ not only in their rights to enter or view certain data, but also in their rights to access certain forms and views. These will be described fully in the EDC system functional specification document section of the Manual of Operations.

**Figure 7. Data Flow and Clarification**

[figure not shown]

### 10.2.2 Database Security

The MS SQL Server database is located on a secure database server. This server is located in a restricted area of the Partners Healthcare server farm and physical access to it is limited to authorized personnel only. Both database and Web servers are located on the Partners Healthcare network behind the firewall. Access to the data at the clinical site will be restricted and monitored through the system's software with its required log-on, security procedures and audit trail. The data will not be altered, browsed, queried, or reported via external software applications that do not enter through the protective system software. There will be a cumulative record that indicates, for any point in time, the names of authorized personnel, their titles, and a description of their access privileges. The record will be in the study documentation accessible at the site. Controls will be in place to prevent, detect, and mitigate effects of computer viruses on study data and software. The application utilizes SSL (Secure Sockets Layer) technology and 128-bit encryption to comply with requirements of 21 CFR Part 11 for Open Systems. Backups of the database will be performed nightly using the services provided by the MGH network. All PC's run virus protection software full-time and are updated with the latest virus detection strings

regularly; the Windows NT server does this as well and has the additional security of scanning all e-mail for viruses before a user can even access them. All accounts are password protected and passwords must be changed on a regular basis.

In addition, the EDC system will have an extra level of password security. At study initiation, the Data Manager will set default passwords for the relevant study personnel at the MGH NCTU and at the study sites. When a new user logs in with the assigned username and default password for the first time, he or she will be forced to change the password to a unique one (at least six characters long), known only to the user. An ongoing paper log will be kept showing when usernames and passwords are set up, for whom, in what user capacity and when usernames are disabled. In case an employee forgets her/his password or a new user is added, they will submit a password request form via email to the Data Manager, who will issue a new default password. They must then go through the Change Password process. The passwords will expire every three months, when users will be required to go through the Change Password process. To avoid password-based software attacks, the system will lock a user for 1 minute if an incorrect password is provided 3 times in a row. A user will also be able to change the password at will if he or she feels that it may have been compromised.

### ***10.2.3 Data Lock Process***

The application will have the ability to lock the database to prevent any modification of data once the study is closed. Once this option is activated, every user will have Read-Only access to the data. Throughout the study, the Study Monitors will be verifying the source documents against the database. The Study Monitors will review source documents and electronic case report forms for accuracy and completeness as described in the study monitoring plan. The Data Manager can only lock the database once the following steps occur: the Site Investigator has signed off on each subject, the Study Monitor has verified the subject's data, and all queries have been resolved. The database will be transferred to the Biostatistics Center by unloading the relational MS SQL Server database to a SAS format for statistical analysis. The database will also be accessible to biostatisticians for reporting and statistical analysis during the trial.

## **10.3 Quality Assurance**

***Study Monitoring.*** Study monitors, supervised by the PI and Co-PIs, will visit each study site at least twice annually to review source documentation materials, informed consent forms, and confirm entered data and that queries have been accurately completed. Study Monitors will also verify that Adverse Events and protocol violations have been reported appropriately to the Coordination Center and their local IRB as required. The Study Monitor will also review clinical facilities resources and procedures for evaluating study subjects and study drug dispensing. Subsequently, the Study Monitor will provide reports of protocol compliance to PI and the Steering Committee. Completed informed consent forms from each subject must be available in the subjects file and verified for proper documentation.

## 10.4 Adverse Experiences Monitoring and Reporting

An adverse event (AE) is any unfavorable and unintended sign (including a clinically significant abnormal laboratory finding, for example), symptom, or disease temporally associated with a study, use of a drug product or device whether or not considered related to the drug product or device.

The adverse event (AE) definitions and reporting procedures provided in this protocol comply with current CFR 21 Part 312 and device regulations CFR 21 Part 812. The Site Investigator will carefully monitor each subject throughout the study for possible adverse events. All AEs will be documented on eCRFs designed specifically for this purpose. It is also important to report all AEs, especially those that result in permanent discontinuation of the investigational drug being studied, whether serious or non-serious.

For the purposes of this study, symptoms of progression/worsening of ALS, including 'normal' progression, will be recorded as adverse events. The following measures of disease progression will not be recorded as adverse events, even if they worsen (they are being recorded and analyzed separately): vital capacity results, HHD results, grip strength results, and ALSFRS-R ratings.

Subjects will be monitored for adverse events from the time they sign consent until completion of their participation in the study. Relationship of adverse experiences to the experimental intervention will be assessed at each in-person and telephone study visit by recording all voluntary complaints of subjects and by assessment of the clinical features of ALS. Attention will be directed to clinical adverse experiences associated with prior ceftriaxone studies, as well as any evidence of unexpected worsening of the underlying ALS. Laboratory surveillance tests will be obtained as outlined above.

A serious adverse event is defined as an adverse event that meets any of the following criteria:

- Results in death
- Is life threatening: that is, poses an immediate risk of death as the event occurred  
This serious criterion applies if the study subject, in the view of the Site Investigator, is at substantial risk of dying from the AE as it occurs. It does not apply if an AE hypothetically might have caused death if it were more severe.
- Requires inpatient hospitalization or prolongation of existing hospitalization.  
Hospitalization for an elective procedure (including elective PEG tube/g-tube/feeding tube placement) or a routinely scheduled treatment is not an SAE by this criterion because a "procedure" or a "treatment" is not an untoward medical occurrence.
- Results in persistent or significant disability or incapacity  
This serious criterion applies if the "disability" caused by the reported AE results in a substantial disruption of the subjects' ability to carry out normal life functions.
- Results in congenital anomaly or birth defect in the offspring of the subject (whether the subject is male or female)

- Necessitates medical or surgical intervention to preclude permanent impairment of a body function or permanent damage to a body structure.

An event is considered "life-threatening" if it places the subject, in the view of the Investigator, at immediate risk of death from the reaction as it occurred; i.e., it does not include a reaction that, had it occurred in a more severe form, might have caused death.

Important medical events that may not result in death, are not life-threatening, or do not require hospitalization may also be considered SAEs when, based upon appropriate medical judgment, they may jeopardize the subject and may require medical or surgical intervention to prevent one of the outcomes listed in this definition. Examples of such medical events include blood dyscrasias or convulsions that do not result in inpatient hospitalization, or the development of drug dependency or drug abuse.

An inpatient hospital admission in the absence of a precipitating, treatment-emergent, clinical adverse event may meet criteria for "seriousness" but is not an adverse experience, and will therefore, not be considered an SAE. An example of this would include a social admission (subject admitted for other reasons than medical, e.g., lives far from the hospital, has no place to sleep).

An unexpected adverse event is any adverse event, the specificity or severity of which is not consistent with the current Investigator's Brochure.

All serious adverse events (SAE) (including death and hospitalization), premature withdrawal, dosage changes and emergency treatment disclosures will be reported to the Coordination Center within one working day and SAE forms completed within 24 hours of their occurrence. The Medical Monitor and DSMB will review all SAE reports. Serious adverse events that occur during this study will be recorded in the subject's chart and on the CRF. All unexpected and related SAEs will be reported to the FDA, Health Canada as required, and to all sites by the Coordination Center. Death due to progression of disease, as expected in ALS, will not be reported in an expedited manner except in cases where the outcome of death is deemed related to study drug.

Sites will be instructed to submit these to their IRBs as well. Additionally, all SAEs will be reported to the FDA annually in the IND report. Any SAE that results in the study being put on hold at any site will be reported to all sites IRB, the NIH and the FDA. All unexpected and related SAEs will be reported to the FDA in an expedited manner, as required by FDA guidelines. Any adverse experiences will be followed for resolution.

There will be ongoing monitoring of non-serious Adverse Experiences through both the EDC system and on-site monitoring visits, to ensure adequate reporting of such events. The MGH Coordination Center will report all AEs to the FDA annually, and sites will be instructed to report AEs as required by their local IRBs. We have included in the Steering Committee two experts in infectious disease, one expert in nephrology, and one expert in gastroenterology, to advise us on how to minimize adverse events from the study drug.

---

#### ***10.4.1 Evaluating and Recording of Adverse Events***

---

At each visit all adverse events that are observed, elicited by the Site Investigator, or reported by the subject will be recorded in the appropriate section of the Adverse Event log, entered into the EDC and evaluated by the Site Investigator.

Minimum information required for each AE includes type of event, duration (start and end dates), severity, seriousness, causality to study drug, action taken, and outcome.

The Site Investigator will grade the severity of AEs. The severity grading will be based on the unique clinical descriptions of severity for each AE in the CTCAE system, which follows this general guideline:

|         |                                  |
|---------|----------------------------------|
| Grade 1 | Mild AE                          |
| Grade 2 | Moderate AE                      |
| Grade 3 | Severe AE                        |
| Grade 4 | Life-threatening or disabling AE |
| Grade 5 | Death related to AE              |

---

The relationship of the AE to the study drug should be specified by the Site Investigator, using the following definitions:

1. Not Related: Concomitant illness, accident or event with no reasonable association with treatment.
2. Unlikely: The reaction has little or no temporal sequence from administration of the study drug, and/or a more likely alternative etiology exists.
3. Possibly Related: The reaction follows a reasonably temporal sequence from administration of the drug and follows a known response pattern to the suspected drug; the reaction could have been produced by the study drug or could have been produced by the volunteer's clinical state or by other modes of therapy administered to the volunteer.
4. Probably Related: The reaction follows a reasonable temporal sequence from administration of study drug; is confirmed by discontinuation of the study drug or by rechallenge; and cannot be reasonably explained by the known characteristics of the volunteer's clinical state.
5. Definitely Related: The reaction follows a reasonable temporal sequence from administration of study medication; that follows a known or expected response pattern to the study medication; and that is confirmed by improvement on stopping or reducing the dosage of the study medication, and reappearance of the reaction on repeated exposure.

---

If discernible at the time of completing the AE log entry, a specific disease or syndrome rather than individual associated signs and symptoms should be identified by the Site Investigator and recorded on the AE log. However, if an observed or reported sign, symptom, or clinically

---

significant laboratory anomaly is not considered by the Site Investigator to be a component of a specific disease or syndrome, then it should be recorded as a separate AE on the AE log. Clinically significant laboratory abnormalities are those that are identified as such by the Site Investigator and/or those that require intervention. The only exception to this will be ALS progression symptoms as previously noted.

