### **2.2.3 Risks of Central Venous Catheters**

In the United States, an estimated five million central venous catheters (CVC) are placed every year [121]. Risks associated with their use vary by catheter type, location of insertion site, hospital size, service and duration of placement [121]. Potential adverse events include local and systemic infection, catheter thrombosis, deep vein thrombosis, pulmonary embolus from either air or thrombosis, anatomical compression of the catheter, pneumothorax, accidental arterial perforation, bleeding, mechanical breakage and accidental removal of the catheter. Some of these complications are more likely to occur at either the time of placement, immediately post placement or with long term placement.

Tunneled catheters, like the Hickman catheter, have a low incidence of serious complications when they are used in the community setting. Rates of systemic infection in the community are 0.34 with each 1000 catheter days [122]. This compares favorably with the CVC bloodstream infection for the inpatient settings, where the incidence is between 2.9 to 5.9 for every 1000 catheter days [123]. Bloodstream infections carry an estimated mortality risk of 10% with each occurrence [124]. Systemic infections that occur early after placement, while the wound remains unhealed, are frequently the result of cutaneous organisms that have migrated along the tunneled

catheter, while infections resulting from contamination of the catheter hub are more likely to occur with prolonged catheter use [125-129].

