### **11.2 Subject Confidentiality**

Confidentiality will be maintained, as all subject research data will be coded with subject ID number and initials. The Coordination Center files will be kept in a secure, double-locked area. The electronic database used during the trial will be secure. To date no breach of our security barriers has occurred, and we actively maintain a high level of security to assess the confidentiality of our databases. Only key personnel in this proposal will have access to the data and the codes. Subject results will never be discussed in any form in the presence of other subjects in the study or with non-laboratory personnel. A subject will be referred to by his/her randomization ID number only. The primary risks of participating in the study are the potential adverse effects from the experimental intervention and the central venous catheter. The PI, Steering Committee, Medical Monitor and Data Safety and Monitoring Board will monitor safety and risks throughout the study. In the rare event that an investigator needs immediate knowledge of the subject's treatment assignment, the individual treatment assignment generated by the Biostatistics Center will be available.

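### Section 10.4.1 records causality only against study drug, so a purely catheter-caused serious event cannot be attributed to the catheter and may not be expedited if its type or severity is unlisted

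*Combined protocol and SAP*

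**What the plan says.** Section 10.4.1 sets the minimum content of an adverse event record. After the event type and dates it lists "severity, seriousness, causality to study drug, action taken, and outcome". The scale is introduced by "The relationship of the AE to the study drug should be specified by the Site Investigator, using the following definitions", and five categories follow. Section 5.1.3 glosses study drug as ceftriaxone or placebo. No item asks about the catheter, its placement or ursodiol.

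Elsewhere the plan takes a wider view:

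- Section 10.4 defines an adverse event as one associated in time with a study, or with "use of a drug product or device whether or not considered related to the drug product or device". It claims compliance with the drug regulations (Part 312) and the device regulations (Part 812).
- Section 11.2 states: "The primary risks of participating in the study are the potential adverse effects from the experimental intervention and the central venous catheter".
- Section 7 lists expected events under three sources: ceftriaxone (7.1), ursodiol (7.2) and the catheter (7.3).

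The expedited rule in section 10.4 reads: "All unexpected and related SAEs will be reported to the FDA, Health Canada as required, and to all sites by the Coordination Center". Section 10.4 judges whether an event is unexpected, in specificity or severity, against the Investigator's Brochure.

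**The concern.** The plan recognises the catheter as a separate and serious source of harm but asks sites to attribute events only to the drug. The catheter is placed for the trial, in both arms, and section 2.2.5 counts the mode of delivery among the risks weighed against benefit.

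Two things are at stake. First, the database will hold no investigator judgement that an event was caused by the catheter. Second, the expedited rule depends on the word related, and the only tool given for deciding that is drug-based. A catheter event of a new type, or of unusual severity, is the kind that other sites and regulators should hear of quickly. It is also the kind most likely to be scored as unrelated to the drug.

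**Working it through.** The plan states no figure to reproduce; this is a question of how the wording operates.

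**1. Run a purely mechanical catheter event through the scale in 10.4.1.** Take a pneumothorax, arterial puncture or air embolus.

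- Definitely Related needs improvement when the drug is stopped or reduced, and recurrence on re-exposure. It does not fit.
- Probably Related needs confirmation by stopping the drug or by rechallenge. It does not fit.
- Possibly Related needs a response pattern already known for the suspected drug. It does not fit.
- Unlikely applies where there is little or no temporal link to the drug "and/or a more likely alternative etiology exists". The catheter is such an alternative, so it fits.
- The first category is "Not Related: Concomitant illness, accident or event with no reasonable association with treatment". It fits if treatment is read as the drug.

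The event therefore lands in one of the two lowest categories.

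**2. Run an event that precedes the first dose.** Section 10.4 collects adverse events from consent. Section 6.2.2 lets the catheter go in before Day 0 and bars randomization of anyone with fever or a significant catheter complication. For these people the drug question has no meaningful answer. They also have no arm, so a safety summary by treatment group (section 9.1.3) leaves them out.

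**3. Look for the object of related in the expedited rule.** The rule gives none. The nearest wording, the exception for deaths from disease progression, speaks of relation to study drug. Section 10.4 also mentions assessing relationship to the experimental intervention, but section 11.2 lists the catheter separately from that. A site following the text would probably use the 10.4.1 scale.

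**4. Ask whether the arm comparison fills the gap.** Section 9.1.3 compares each adverse event between arms. Both arms have the catheter, so harm common to both largely cancels from the difference.

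**5. Context on how much catheter harm to expect.** Inputs: 0.34 systemic infections per 1000 catheter days and 10% mortality per infection (2.2.3: "Bloodstream infections carry an estimated mortality risk of 10% with each occurrence"); 600 subjects (3.1); 18 months' average on-treatment follow-up (6.3.4). The 12- and 24-month rows are assumptions to show a range. Catheter days = 600 × months × 30.4375; infections = days × 0.34/1000; deaths = infections × 0.10.

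| Average catheter time | Catheter days | Infections | Deaths |
|---|---|---|---|
| 12 months | 219,150 | 74.5 | 7.5 |
| 18 months | 328,725 | 111.8 | 11.2 |
| 24 months | 438,300 | 149.0 | 14.9 |

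Arterial puncture at 1% to 8.4% (2.2.3) gives 600 × 0.01 = 6 to 600 × 0.084 = 50 subjects.

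**The case against.** A reader might infer that catheter harm is unrelated by definition and that the expedited rule can never apply to it. The documents do not support that.

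- An infection during long-term antibiotic treatment could be scored Possibly Related, since section 7.1 lists superinfection and candidiasis as drug effects and that category allows for competing therapies.
- The expedited rule leaves related undefined, in a section that covers devices and cites Part 812. That is ambiguity, not exclusion.
- Section 10.4.1 sets minimum content. The case report form and Manual of Operations, which might hold a catheter item, are not among the documents.

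Expectedness may decide most cases first. Section 7.3 lists line infection, thrombosis, pulmonary and air embolus, pneumothorax and arterial puncture. The formal reference is the Brochure, which is not available here, and severity counts as well as type. So listing does not settle an unusually severe case.

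Oversight does not depend on causality. All serious events go to the Coordination Center within one working day, to the Medical Monitor and DSMB for review, and to the FDA annually (10.4). Section 11.1 also has the PI report adverse events to the FDA, DSMB and site investigators without a causality filter.

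It would also go too far to say that the final report cannot separate drug harm from delivery harm. Event type is recorded, many catheter events identify themselves, and the placebo arm shows catheter harm without ceftriaxone. Ambiguous events, such as sepsis or a death with several possible causes, still lack a recorded judgement.

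These points narrow the concern. They do not supply the missing attribution or say what related refers to.

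**Conclusion.** The point stands as a gap in attribution and an ambiguity in the expedited rule. Causality is specified only for the drug. A serious event caused purely by the catheter or its placement, including one before the first dose, would probably be scored Not Related or Unlikely. It might then not be expedited if its type or severity is unlisted. The by-arm comparison does not isolate this harm either.

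The loss is confined to attribution and to expedited notice of unlisted or unusually severe catheter events. The number of such events cannot be derived from the documents. The 75 to 149 infections, 7 to 15 deaths and 6 to 50 punctures show only that catheter harm will not be rare; most are listed event types.

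Those figures assume a catheter in place throughout follow-up. The mortality figure is also uncertain here: the title of its cited review concerns noncuffed catheters, while this trial uses a tunneled, cuffed one. The upper puncture rate may be too high, because section 2.2.3 suggests that the lower rate may go with the jugular route, which the trial uses. The conclusion further assumes that no catheter item exists in forms outside these documents.

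**What to change.** - **Section 10.4.1:** add a separate item for relationship to the catheter or its placement, beside the study drug item. A similar item for ursodiol or its placebo is optional.
- **Section 10.4:** state that, for expedited reporting, related means related to study drug or to the catheter or its placement. Name the reference against which catheter events are judged expected, for example section 7.3 together with the Brochure.
- **Section 9.1.3:** tabulate catheter-related serious events and deaths pooled across arms, including those before randomization.

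The cost is one extra eCRF field (two with ursodiol), a paragraph of protocol text and a short training note to sites. The downside is a few more expedited reports. Clinical management and the efficacy analyses are unchanged.
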